#### Aim 2 – moderation

##### RCP method

A total sample size of 480 observations, were obtained by sampling 3 level-2 units (PHD) in the control group, 3 level-2 units (PHD) in I only group, 3 level-2 units (PHD) in the E only group, and 3 level-2 units (PHD) in the E+I group. Finally, 40 level-1 units (individuals with repeated measurements) were obtained from each level-2 unit (PHD). This sample achieves >90% power to detect a three-way interaction among the subject-specific slopes of at least 3.0. A test based on a mixed-model analysis assuming random slopes will be used. This test will be conducted at a significance level of 0.05.

##### LMS method

A total sample size of 492 level-1 units (individuals), which were obtained by sampling 3 level-2 units (PHD) in the control group, 3 level-2 units (PHD) in I only group, 3 level-2 units (PHD) in the E only group, and 3 level-2 units (PHD) in the E+I group, with an average of 41 level-1 units (individuals) per level-2 unit (PHD), achieve >85% power to detect an interaction difference among the group means of at least 3.75. A test based on a mixed-model regression analysis at a significance level of 0.05.

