#### Aim 2: mediation/moderation

We will evaluate the mediator effects of motivation, self-efficacy, neighborhood walkability, support from HLAs, and fidelity and moderator effects (i.e., sleep, financial strain, public housing development characteristics, neighborhood social cohesion, and access to physical activity resources) on physical activity behavior.

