### Sample size

#### Aim 1 - within group analysis sample size

A sample size of 21 achieves 90% power to detect a mean of paired differences of 3.0 with a significance level of 0.05 using a two-sided paired t-test. A sample size of 34 achieves >90% power to detect a difference of 3.0 with a significance level of 0.05 using a two-sided Wilcoxon Signed-Rank test. Assuming at least 20% of the sample changes between baseline and follow-up a sample size of 115 pairs achieves 80% power to detect an odds ratio of 3.0 using a two-sided McNemar’s test with a significance level of 0.05. The odds ratio is equivalent to a difference between two paired proportions of 0.10.

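### The power figure under Aim 2 moderation (LMS method) describes the E x I interaction of Hypothesis 3 and covers no moderator

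*Protocol article*

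**What the plan says.** The LMS paragraph of the sample-size section (Aim 2, moderation) takes 3 developments in each of the four arms and an average of 41 residents per development, 492 in all. It claims that these "achieve >85% power to detect an interaction difference among the group means of at least 3.75". It adds only: "A test based on a mixed-model regression analysis at a significance level of 0.05".

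The section Aim 2: mediation/moderation says what is to be tested: "moderator effects (i.e., sleep, financial strain, public housing development characteristics, neighborhood social cohesion, and access to physical activity resources"). Table 1 classes sleep, financial strain and social cohesion as individual-level measures. It classes development characteristics and access to resources as environment-level.

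The interaction between the two interventions appears elsewhere. Under Aim 1, Hypothesis 3 is the synergy hypothesis, and its analysis paragraph tests the E-by-I interaction in a multilevel regression. The Aim 1 sample-size paragraphs cover within-group change and a comparison of two group means. Neither covers Hypothesis 3.

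**The concern.** A power statement has to belong to the test it is printed under. Moderation asks whether the effect of an arm differs by the level of a third variable, so its power depends on that variable's distribution and on the size of an arm-by-moderator term. The LMS sentence has neither. Its only ingredients are the four arms and their means.

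Two things are at stake. A null moderator result could be read as coming from an analysis with more than 85% power, when no such power has been shown. And the synergy hypothesis, which is the reason for a factorial layout, has no power figure of its own, although one that fits it stands under another aim.

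**Working it through.** **1. Which test the figure fits.** Four arms (control, E, I, E+I) form a 2x2 layout. The interaction among their means is (E+I − E) − (I − C), which is the Hypothesis 3 contrast. None of the five moderators listed for Aim 2 appears in the sentence.

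**2. Inputs for checking the number.**
- From the LMS paragraph: k = 3 developments per arm, m = 41 residents each (12 x 41 = 492), difference 3.75, alpha 0.05. Two-sided testing is assumed, as in the within-group paragraph.
- SD: not stated. The only recoverable value comes from the within-group paragraph: "A sample size of 21 achieves 90% power to detect a mean of paired differences of 3.0". With SD 4, a paired t-test has 90.5% power at n = 21 and 88.9% at n = 20, so SD is about 4. That is an SD of paired differences and may not be the one used here.
- ICC: not stated. Assumed, with a range shown.
- Degrees of freedom: 12 developments − 4 arms = 8.

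**3. Reproducing the figure.** The variance of the contrast is 4 x SD² x [1 + (m − 1) x ICC] / (k x m). With SD 4 and ICC 0.05:
- Design effect = 1 + 40 x 0.05 = 3.0.
- SE = 4 x √(4 x 3.0 / 123) = 1.249.
- 3.75 / 1.249 = 3.00.
- Normal reference: Φ(3.00 − 1.96) = 85.1%. At m = 40 it is 84.8%.
- Non-central t on 8 df: 74.8%. At 85% power the detectable difference would be about 4.28.

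The plain E x I contrast can thus produce the printed figure, which supports step 1.

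**4. The match is not unique.** With SD 3.5 and ICC 0.05, SE = 3.5 x √(12 / 123) = 1.093 and 3.75 / 1.093 = 3.43. On 8 df that gives 85.1% at m = 41 and 84.8% at m = 40. This is the same pair of values, with the cluster degrees of freedom respected.

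Power for 3.75 at SD 4, m = 41:

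| ICC | Normal reference | 8 df |
|---|---|---|
| 0.02 | 97.2% | 92.2% |
| 0.03 | 93.9% | 86.5% |
| 0.05 | 85.1% | 74.8% |
| 0.10 | 64.2% | 53.3% |

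**5. A statement that needs neither SD nor ICC.** If a large-sample reference gave 85%, then difference/SE = 1.96 + 1.04 = 3.00, and power on 8 df is 74.7%. If it gave 90%, power on 8 df is 81.0%.

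**6. Why the figure cannot stand in for moderator power.** Using the same assumed SD 4 and ICC 0.05, 123 per arm and a difference of 3.75:
- Individual-level binary moderator split 50/50, two arms compared: SE = 4 x √0.95 x √(4 / 61.5) = 0.994, power 96.5% (normal reference).
- The same moderator in a three-way E x I x moderator term: SE = 4 x √0.95 x √(8 / 61.5) = 1.406, power 76%.
- Development-level moderator with 12 values and 3.75 per SD of the moderator, by simulation on development means with variance 16 x (0.05 + 0.95/41) = 1.17: about 48% with a separate slope in each arm (8 parameters, 4 df), and about 85% with one pooled E-by-moderator slope. For 2 per SD the values are about 21% and 47%.

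The answer runs from about 48% to above 96%, depending on the moderator's level and the term fitted. The LMS sentence fixes neither.

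**The case against.** **The figure may be sound for E x I.** A reader might infer that it is overstated and that true power is 75%. The documents do not support that. SD and ICC are not given, the SD of 4 is borrowed from a paired comparison, and step 4 shows a calculation on the correct 8 df that yields the same 85.1% and 84.8%. It can be argued that an ICC of 0.05 with SD 4 is the more natural explanation of why 41 residents were chosen, but SD 3.5 with the same ICC explains it equally well. This objection stands: the 75% is conditional.

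**Unstated SD and ICC may be in the full protocol.** The article cites a protocol version that is not shown, so their absence is no fault in itself. Accepted. The point rests on what the sentence says it powers.

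**The sentence may be shorthand.** The LMS method forms latent interactions among random coefficients, so a moderator could sit behind the calculation. If so, the sentence still describes a contrast of arm means and needs correcting.

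**Moderation may be well powered anyway.** For individual-level moderators this may be true, as step 6 shows. It would be wrong to conclude that all moderator tests are weak, and the low values for development-level moderators depend on a model the article does not specify.

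**The RCP figure.** A reader might extend the criticism to the neighbouring claim, "This sample achieves >90% power to detect a three-way interaction among the subject-specific slopes of at least 3.0". That does not follow. It concerns a different model with repeated measurements, the article defines RCP as predicting a random slope from a moderator, and no calculation here tests it. It is not shown to be wrong.

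**Conclusion.** The LMS power figure is attached to the wrong test. As worded it is for the E x I interaction of Hypothesis 3. It gives no power for any Aim 2 moderator by the LMS method, and Hypothesis 3 has no power statement under its own heading. This rests on the text and the 2x2 layout alone and needs no assumed input.

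The correctness of the figure for E x I is open. If a large-sample reference was used, 85% falls to about 75% on 8 degrees of freedom. If the 8 degrees of freedom were already used, for example with SD 3.5 and ICC 0.05, it stands. Aim 2 is not the primary aim, and the article already acknowledges the small number of clusters and plans residual bootstrap intervals. The consequence is therefore misreading of moderator results and an unstated basis for Hypothesis 3. The primary comparison is not affected.

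**What to change.** - Move the LMS figure to Hypothesis 3 as power for the E x I interaction. Restate it with its unit, SD, ICC and a reference distribution on the 8 between-development degrees of freedom, recomputed from the sponsor's own inputs.
- Under Aim 2 moderation, LMS method, delete the claim of more than 85% power, or replace it with power for a stated arm-by-moderator term. Give this separately for individual-level moderators (sleep, financial strain, social cohesion) and for development-level moderators (development characteristics, access to resources), which have only 12 values each. State the model used for the latter.
- No change to the RCP figure is asked for on this evidence.

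Cost: a wording change and one recalculation. The stated power may become less favourable. No extra participants or developments are needed.

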#### Aim 3 - qualitative interviews

We will conduct qualitative interviews with 40 key informants to explore the future implementation of the multilevel physical activity intervention using the Consolidated Framework for Implementation Research as our conceptual model [73]. We will purposefully sample key informants across multiple organizational levels to obtain the most relevant information. Sources will include HLAs, advisory board members, public housing development managers, and representatives from WalkMassachusetts, the Boston Housing Authority, the Boston City Health Department, and from Housing and Urban Development (the organization that administers public housing in the U.S.). Our guiding principle in sample size selection is purposeful sampling, which is used to gain information from information-rich cases intentionally selected to inform the research question.

Interviewers will follow a semi-structured interview guide with sections corresponding to each of the five CFIR domains: Outer Setting, Inner Setting, Intervention Characteristics, Characteristics of Individuals, and Process. The guide will allow for structured questions to be asked in all interviews, while allowing flexibility to probe or follow up on emerging topics. Interviews will be audiotaped, transcribed verbatim, and systematically read as they are being conducted to determine if information saturation has been reached. We will conduct a content analysis of the transcripts [74]. We will draw from the questions in our interview guide to create a preliminary coding framework. A staff member will independently code the transcripts according to the preliminary coding framework, adding additional codes as needed to cover emerging topics.

Interview themes will also be compared among those public housing developments in which key informants gave higher and lower organizational readiness ratings during the housing manager interviews conducted at baseline. Then, following team-based coding, the preliminary coding structure will be shown to the entire research team to review our analysis decisions. Codes will be added, refined, and deleted during this process. To enhance the trustworthiness of the analysis, we will hold at least two peer debriefing meetings with the entire research team to show them the transcripts and the codes applied and ask for their feedback [75]. Any discrepancies will be resolved through team discussion. Codes will then be summarized into themes. We will use NVIVO qualitative software to assist in data management.

## Discussion

The Community Walks study addresses a gap in the literature to test multilevel interventions in low-income populations and is nearly unique in its focus on this population, on a layered multilevel design, and on walking as the main form of physical activity. The environmental level intervention will be delivered by community residents trained as HLAs for leading walks using newly designed and marked walking trails around the development. Among residents randomized to the I and E+I condition, we will enroll interested residents to a more intensive individual level eHealth phone intervention to further promote motivation and self-efficacy for physical activity.

As described by Hall and colleagues, a continuum exists ranging from fundamental multilevel research to multilevel intervention research [29]. The Community Walks study represents an example of multilevel intervention research which “intervenes at two or more levels, measures factors at 2 or more levels, and examines interactions between levels” [29]. This type of research is designed to “inform decision making regarding levels, intervention components, and targets” [29]. Therefore, with our findings, we expect to contribute to a greater understanding of whether an individual or environmental intervention that includes an eHealth program and walking groups/trails and maps/and advocacy training are important drivers for physical activity promotion among urban public housing residents. This study will join other similar studies in contributing to this evidence base of multilevel physical activity trials, including the Steps for Change (on-going) – a trial testing a physical activity promotion program across personal, social, and physical environment domains among residents of senior public housing and developments [36]. The study will also add to the evidence base of community physical activity trials focused on walking groups, such as Positive Action for Today’s Health – a trial testing the efficacy of walking groups plus social marketing program [76].

The interviews we have planned at the conclusion of the trial will help us understand barriers and facilitators to intervention reach, adoption, implementation and maintenance, which will inform future intervention efforts. Other research teams have also included qualitative methods of intervention evaluation, including participatory evaluation (e.g., Ripple Effects Mapping) to elucidate factors most important to participants and other stakeholders [77]. Therefore, we expect the qualitative interviews to elucidate our trial findings and inform future directions of this work, which has implications for federal- and state-funded public housing developments nationwide. It is imperative to understand barriers and facilitators of uptake and adoption of health promotion programs, such as the Community Walks study in order to determine how to apply clinical trial findings to larger housing development networks, thereby achieving high public health impact [78].

Limitations of our study should be considered. Because our primary outcome is measured by actigraphy, those who are not able to ambulate independently are not included in the evaluation cohort. However, we do allow those using certain assistive devices (such as walkers) to participate in the evaluation cohort, as we thought actigraphy would be appropriate in these instances. In addition, only those willing to participate are included in the evaluation cohort. These may create bias in our sampling frame. Our program is available in English and Spanish, which represents most languages spoken in public housing developments. However, while people who speak other languages will be welcome to participate in E level intervention activities, they may not feel as welcome or be able to participate fully. Finally, the study is conducted in only one city, which may limit external generalizability.

In conclusion, a multilevel, multicomponent community-based study is being conducted to test whether individual- and environmental-level intervention programming promotes moderate intensity physical activity among urban public housing residents.

## Trial status

Protocol Version 1.8, June 7, 2023.

Recruitment Start Date: May 2, 2022.

Recruitment Approximate End Date: September 4, 2023.

## Data Availability

[name], [name], and [name] have Access to the final trial dataset. No contractual agreements limit access to dataset. The datasets generated and/or analyzed during the current study are not publicly available due to the research is still ongoing, but are available from the corresponding author on reasonable request. Participant recruitment for this trial is not completed and is still ongoing.

## Abbreviations

E: Environmental
E + I: Environmental + Individual
I: Individual
HLA: Healthy Living Advocate
RCP: Random Coefficient Prediction
LMS: Latent Moderated Structural Equation
PHD: Public Housing Development
IRB: Institutional Review Board
TSRQ: Treatment Self-Regulation Questionnaire
APGAR: Adaptation, Partnership, Growth, Affection, and Resolution
CESD: Center for Epidemiologic Studies Depression Scale
